## 2. AIM OF THE STUDY:

The aim of this study is to evaluate the efficiency of fluoxetine as an adjuvant therapy in the treatment of severe sepsis and its effect on multiple organ dysfunction and mortality in septic patients.

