## Patients and Methods:

### Study Population:

- ASA II, III 60 patients, aged 18-65 years, BMI 30-35, admitted to ICU and diagnosed as patients with severe sepsis.
- The diagnosis of severe sepsis was established according to the definitions of the Surviving Sepsis Campaign (SSC) (**Singer et al., 2016**).

**Severe sepsis definition = sepsis-induced tissue hypoperfusion or organ dysfunction (any of the following thought to be due to the infection)**

Sepsis-induced hypotension

Lactate above upper limits laboratory normal

Urine output  $< 0.5 \text{ mL/kg/hr}$  for more than 2 hrs despite adequate fluid resuscitation

Acute lung injury with  $\text{Pao}_2/\text{Fio}_2 < 250$  in the absence of pneumonia as infection source

Acute lung injury with  $\text{Pao}_2/\text{Fio}_2 < 200$  in the presence of pneumonia as infection source

Creatinine  $> 2.0 \text{ mg/dL}$  ( $176.8 \text{ }\mu\text{mol/L}$ )

Bilirubin  $> 2 \text{ mg/dL}$  ( $34.2 \text{ }\mu\text{mol/L}$ )

Platelet count  $< 100,000 \text{ }\mu\text{L}$

Coagulopathy (international normalized ratio  $> 1.5$ )

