- **Group 2:** Receiving conventional sepsis therapy in addition to fluoxetine 40 mg ( Prozac 20mg , Elli Lillys medical company Indianapolis, Indiana, United States) ® (1) daily for 28 days or until discharge from the ICU or death.
- **Primary outcome:** vasopressor dose.
- **Secondary outcome:** ICU Mortality & Organ dysfunction.

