### Statistical Analysis and Sample Size:

- Data entry, processing, and statistical analysis will be carried out using SPSS v29. Frequency tables with percentages will be used for categorical variables and descriptive statistics (mean  $\pm$  standard deviation or median with interquartile range) will be used for numerical variables. Tests of significance (Chi-square, student's t-test, or Mann Whitney's test) will be used according to the normality of the data. A P-value of less than 0.05 will be considered statistically significant. Total sample size 52 cases (organ dysfunction using SOFA score will be used as a primary outcome with proposed large effect size (0.8) and  $\alpha=0.05$  and power=0.80, so, 26 cases are needed in each group).

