### Sample Size Calculation:

- The sample size was based on a meta-analysis by Rygård et al. (9), which reported a mean reduction in shock duration of  $-1.52$  days with corticosteroids compared to placebo (95% confidence interval:  $-1.71$  to  $-1.32$ ). Using this effect size, a two-sided alpha of 0.05, and 80% power, we calculated that 23 patients per group (46 total) would be sufficient to detect a statistically significant difference.

Reference: **Rygård SL, Butler E, Granholm A, Møller MH, Cohen J, Finfer S, Perner A, Myburgh J, Venkatesh B, Delaney A.** Low-dose corticosteroids for adult patients with septic shock: a systematic review with meta-analysis and trial sequential analysis. *Intensive Care Med.* 2018 Jul;44(7):1003-1016. doi: 10.1007/s00134-018-5197-6. Epub 2018 May 14. PMID: 29761216.

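### Two different outcomes are named primary (vasopressor dose and SOFA), neither sample-size calculation concerns vasopressor dose, and the totals 60, 52 and 46 are not reconciled

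*Protocol*

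**What the plan says.** Five places in the protocol bear on this point.

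- **Outcome list, after the description of Group 2:** "Primary outcome: vasopressor dose", followed by "Secondary outcome: ICU Mortality & Organ dysfunction".
- **Statistical Analysis and Sample Size:** "Total sample size 52 cases", with the reason that "organ dysfunction using SOFA score will be used as a primary outcome with proposed large effect size (0.8"), at alpha 0.05 and "power=0.80, so, 26 cases are needed in each group".
- **Sample Size Calculation:** a meta-analysis of corticosteroids against placebo gave a mean difference in shock duration of -1.52 days. From this, at two-sided alpha 0.05 and 80% power, "we calculated that 23 patients per group (46 total) would be sufficient to detect a statistically significant difference".
- **Study Population:** "ASA II, III 60 patients, aged 18-65 years, BMI 30-35, admitted to ICU". No calculation or loss allowance is attached to the 60.
- **Aim of the Study:** the efficiency of fluoxetine as adjuvant therapy in severe sepsis and "its effect on multiple organ dysfunction and mortality in septic patients".

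Shock duration is not in the outcome list. The nearest item is the duration of vasopressor and inotropic support under Clinical Data.

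**The concern.** Organ dysfunction is secondary in one current section and primary in another. A statistical analysis plan that followed either section would contradict the other, so the conflict has to be resolved in the protocol itself.

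Two things are at stake. First, a significant result on either vasopressor dose or SOFA could be reported as the primary result with support in the text, so P<0.05 would no longer carry a 5% error rate. Second, both 80% power statements belong to other quantities (SOFA and shock duration). The outcome in the explicit declaration has no effect size, standard deviation or power statement.

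**Working it through.** **1. The statements side by side**

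| Section | Quantity | Called primary? | Total |
|---|---|---|---|
| Outcome list | Vasopressor dose | Yes | none derived |
| Outcome list | Organ dysfunction | No, secondary | none derived |
| Statistical Analysis and Sample Size | Organ dysfunction (SOFA) | Yes | 52 |
| Sample Size Calculation | Shock duration | No | 46 |
| Study Population | none | not applicable | 60 |

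Two outcomes are called primary. A third quantity is only the basis of a calculation.

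**2. Reproducing the 52.** Inputs from Statistical Analysis and Sample Size: d = 0.8, alpha 0.05 (taken as two-sided), power 0.80.

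- Normal approximation: n per group = 2(1.960 + 0.842)²/d² = 2 × 7.85/0.64 = 24.5, so 25.
- Two-sample t-test (noncentral t): n = 25.5, so 26 per group and 52 in total. Power at 26 per group is 80.7%.

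The 52 is correct for its own inputs and for a plain two-sample t-test.

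**3. Trying to reproduce the 46.** The formula is n per group = 2·SD²(1.960 + 0.842)²/1.52². The section gives no SD, so the figure cannot be checked. Solving backwards, 23 per group needs d = 0.845 by the t-test, which implies SD = 1.52/0.845 = 1.80 days. The normal approximation gives d = 0.826 and SD = 1.84 days. With assumed SDs of 2, 3 or 4 days, the requirement would be 28, 62 or 109 per group (normal approximation).

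**4. Power for vasopressor dose.** There is no stated figure to reproduce. Taking all 60 patients as 30 per group, with no losses and a two-sided t-test, 80% power is reached at a standardised difference of 0.736, or about 0.74. Over an assumed range of true standardised differences:

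| Assumed d | Power, 30 per group |
|---|---|
| 0.4 | 33% |
| 0.5 | 48% |
| 0.6 | 63% |
| 0.8 | 86% |

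**5. False-positive rate if either named primary may be claimed.** The rate is 1 − P(|Z₁| < 1.96 and |Z₂| < 1.96) when fluoxetine affects neither outcome.

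- Independent: 1 − 0.95² = 0.0975, or 9.8%.
- Assumed correlation 0.5: about 9.1% (bivariate normal).
- Assumed correlation 0.7: about 8.4% (bivariate normal, 8.35%).

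The protocol gives no correlation; these two values are assumptions.

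**6. The totals.** 60 exceeds 52 by 8 and 46 by 14. Losses of 8/60 = 13.3% or 14/60 = 23.3% would connect them, but the protocol states neither.

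**The case against.** The strongest reply is that the outcome list is the formal declaration and settles the matter, that the sizing paragraphs only justify feasibility, and that 60 patients exceed both calculated totals. Part of this stands, and it rules out several stronger readings that a reader might infer.

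- **Three primary endpoints.** A reader might count shock duration as a third and quote 1 − 0.95³ = 14.3%. The text never calls it primary and does not list it as an outcome, so the two-outcome rate is the supported one.
- **Underpowering shown by the differing totals.** It is not. The 60 is an unexplained enrolment count, not a size computed for vasopressor dose, and it lies above both calculated totals. At d = 0.8, 30 per group gives 86%.
- **Loss of power at 23 per group.** Power at d = 0.8 would be 75.6%, but that applies the SOFA effect size to a sample sized on another quantity, and 46 is not the planned enrolment.
- **An aim that excludes vasopressors.** The aim also speaks of efficiency in treating severe sepsis, which is broad enough to cover vasopressor need. Its silence on vasopressors is weak evidence.

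What does not stand is the premise that the sizing text is neutral. Statistical Analysis and Sample Size says outright that SOFA organ dysfunction is used as a primary outcome, which directly contradicts its secondary rank in the outcome list.

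**Conclusion.** The contradiction is real and needs correction. Two outcomes are named primary, a third quantity underlies a second calculation, and the three totals are not connected. The stated 80% power does not apply to vasopressor dose.

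The inflation is from 5% to 9.8% if the two named primaries are independent, and to about 9.1% or 8.4% at the assumed correlations. These rates hold only if success on either outcome would be claimed as the primary result. The text permits that but does not say it is intended.

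Actual power for vasopressor dose is unknown, because the protocol gives no effect size or SD for it. The finding is that the power claim has no basis for this outcome, not that the trial is shown to be too small.

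**What to change.** Before any unblinded data are seen, amend the protocol as follows. The choice of primary is the sponsor's.

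1. Name one primary outcome, with one summary measure and one time point, identically in the outcome list and in both sample-size sections. Make the other outcome secondary.
2. Keep only the sample-size statement that belongs to the chosen primary, and state one total. If that total is 60, give the sponsor's own reason for exceeding the calculated size.
3. **If SOFA is chosen:** keep the d = 0.8, 26-per-group calculation, delete the shock-duration one, and fix the analysis day. SOFA is scored only until ICU discharge, death or day 28, so state how both death and ICU discharge before the analysis day are handled. The 26 reproduces for a plain two-sample t-test; a baseline-adjusted or ranked analysis would need its own justification.
4. **If vasopressor dose is kept:** delete both calculations and state that 30 per group (no losses, t-test) gives 80% power only for a standardised difference of about 0.74. Any one of several organ-dysfunction criteria suffices for entry, and vasopressors are started only when fluids fail. Some patients may therefore have zero dose, which may make the t-test figure optimistic.

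The cost is an amendment to the primary outcome, which is more than an editorial change, and a less favourable power statement if vasopressor dose is kept. No additional patients are needed.

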## Procedures:

### Clinical Evaluation:

- History and physical examination with special emphasis on vital signs (Blood pressure, pulse, Temperature, Respiratory Rate) and Glasgow Coma Scale to be continuously evaluated. drug to interaction will be considered when addi new drugs like the amino acids L-dopa and L-tryptophan, anorexiant, anticonvulsants, antidepressants, anxiolytics, calcium channel blockers, cyproheptadine, lithium salts, and drugs of abuse.
- Basl line ECG and calculation of QR interval and detection of ant type of arrythemia by cardiologist then follow up every otherday
- 10 ml blood sample will be taken there will be no leftovers and no sample storage after research ends and the following labartory parameters will be measursed

### Routine Laboratory Investigations:

- CBC (Complete blood count)
- Coagulation profile: PT, INR, PTT
- ABGs (Arterial Blood Gases)
- Central Venous Oxygen Saturation
- Liver Function Tests: ALT (Alanine aminotransferase), AST (Aspartate aminotransferase), TBL (Total bilirubin), albumin
- Kidney Function Tests: urea, serum creatinine
- These routine labs will be withdrawn daily.

### Labs Specific for the Study:

[figure not shown][figure not shown][figure not shown]

- Lactate
- CRP (C-reactive protein)
- Procalcitonin
- On days 1, 3, 7, 10, and 14.

### **Microbiological Studies:**

- Including cultures (sputum, blood, urine or biological fluid according to clinical suspicion) on day 1.

### **Imaging Studies:**

- Required to identify the source of sepsis (e.g., pelvi-abdominal CT, ultrasound, chest x-ray).

### **Clinical Data:**

- To be evaluated up to a maximum follow-up period of 28 days of ICU stay:
  - Length of hospital stay
  - Need for and duration of mechanical ventilation
  - Need for and duration of vasopressor and inotropic support
  - Need for hemodialysis
  - Final outcome:
    - Survivors:
      - A) Patients recovered and discharged from ICU.
      - B) Patients still morbid and stayed in ICU more than 28 days.
    - Non-survivors:
      - Death before the completion of the 28 days of study period.

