### **Application of APACHE II and SOFA Scoring Systems:**

- APACHE II score to be evaluated on study day 1.

- SOFA score to be evaluated on study day 1 and serially every day until ICU discharge or death or up to 28 days.

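### Mortality is not defined consistently: the outcome line says ICU mortality, the survivor and non-survivor classes overlap and leave a gap, and no vital status after ICU discharge is planned

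*Protocol*

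**What the plan says.** The aim (section 2) is to study fluoxetine in severe sepsis and "its effect on multiple organ dysfunction and mortality in septic patients". The secondary outcome line, after the description of Group 2, reads "ICU Mortality & Organ dysfunction" and adds neither a time horizon nor a definition.

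The only operational definition is under Clinical Data, Final outcome. The list there opens with "To be evaluated up to a maximum follow-up period of 28 days of ICU stay". It then gives two survivor classes, "A) Patients recovered and discharged from ICU" and "B) Patients still morbid and stayed in ICU more than 28 days", and one non-survivor class, "Death before the completion of the 28 days of study period".

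Other observation stops when the patient leaves the ICU. Fluoxetine is given "daily for 28 days or until discharge from the ICU or death", and SOFA is scored "serially every day until ICU discharge or death or up to 28 days". Length of hospital stay is listed among the clinical data, but the protocol describes no check of vital status after ICU discharge.

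**The concern.** The outcome line ties mortality to the ICU. The non-survivor class ties it to a 28-day period and does not restrict the place of death. The survivor classes depend on whether the patient has left the ICU, and one of them also on recovery. Two analysts could follow this text faithfully and report different numbers of deaths.

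The reading that removes most of the conflict, death in the ICU within 28 days, has a weakness of its own. ICU discharge happens after randomisation and is a clinical decision. If treatment changes how soon patients leave, it can change where they die without changing whether they die. A difference in ICU mortality would then partly reflect discharge timing. A later analysis plan could choose one definition, but it could not recover ward deaths that the protocol never arranged to collect.

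**Working it through.** **Step 1. Classify patient paths under each wording.** No assumption is needed.

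| Path | Outcome line (ICU mortality) | Clinical Data classes, as written | Death in ICU within 28 days |
|---|---|---|---|
| Recovered, leaves ICU day 10, dies on ward day 18 | not a death | survivor A and non-survivor | survivor A |
| Leaves ICU alive but not recovered, alive at day 28 | not a death | no class | not a death, still no class |
| Dies in ICU day 33 | death if no limit applies | survivor B | survivor B |
| Dies in ICU day 12 | death | non-survivor | death |
| Recovered, leaves ICU, alive at day 28 | not a death | survivor A | survivor A |

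The last two paths are consistent. The day-33 path is settled if the opening line of Clinical Data governs. The first path is settled on that reading only by counting a death before day 28 as survival. The second stays without a class on any reading.

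**Step 2. Size of the dependence on discharge timing.** The protocol gives no mortality figure to reproduce. Both of its sample size calculations concern other outcomes (SOFA, 52 patients; shock duration, 46 patients).

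Inputs:
- 60 patients (Study Population). Equal allocation is an assumption, giving 60 / 2 = 30 per arm.
- True 28-day mortality m, the same in both arms: assumed 30%, range 20% to 40%.
- Share s of those deaths that occur after ICU discharge: assumed 10% in control and 10% to 50% with fluoxetine.
- Test: chi-square, as in Statistical Analysis, at 0.05. It is taken without continuity correction, and rejection rates come from exact binomial enumeration.

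Formulas: ICU mortality within 28 days = m × (1 − s). False difference = m × (s for fluoxetine − s for control).

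For m = 0.30 and control s = 0.10, control ICU mortality is 0.30 × 0.90 = 27%:

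| s, fluoxetine | ICU mortality, fluoxetine | False difference | Rejection rate |
|---|---|---|---|
| 10% | 0.30 × 0.90 = 27% | 0 points | 4.9% |
| 20% | 0.30 × 0.80 = 24% | 3 points | 5.7% |
| 30% | 0.30 × 0.70 = 21% | 6 points | 8.2% |
| 40% | 0.30 × 0.60 = 18% | 9 points | 12.9% |
| 50% | 0.30 × 0.50 = 15% | 12 points | 20.2% |

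Range over m: at 10% versus 20% the false difference is 0.20 × 0.10 = 2 points to 0.40 × 0.10 = 4 points. At 10% versus 50% it is 0.20 × 0.40 = 8 points to 0.40 × 0.40 = 16 points.

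With equal shares of 10% there is no false difference, but 30 × 0.30 × 0.10 = 0.9 deaths per arm are lost.

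**Step 3. Weight of one patient.** One reclassified death moves an arm's mortality by 1 / 30 = 3.3 points, or by 1 / 26 = 3.8 points at the 26 per group of the SOFA calculation.

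**The case against.** The strongest reply is that the opening line of Clinical Data governs everything below it, including the final outcome. A non-survivor is then a patient who dies in the ICU within 28 days. This agrees with the name ICU mortality and with treatment and SOFA both stopping at ICU discharge, death or 28 days. It answers one thing a reader might infer, that ICU mortality has no time limit and so a death in the ICU on day 33 is a plain contradiction. The documents do not support that as a firm finding, because the opening line can supply the limit. It does not settle the rest. The non-survivor line itself refers to the study period and not to the ICU, a patient discharged unrecovered still has no class, and discharge still ends the count.

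A second reply is that double classification and uncollected ward deaths cannot both occur in full. If observation ends at ICU discharge, ward deaths go unrecorded and nobody is counted twice. If hospital stay is followed, as its listing suggests, some ward deaths will come to notice. This stands, so no number of doubly classed patients can be given.

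A third reply is that the bias is assumed. Nothing in the documents indicates that more deaths would follow discharge in one arm, and the protocol calls the trial double-blind. This also stands for the size. It does not remove the mechanism, since under perfect blinding a drug effect on recovery time could still move discharge.

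Finally, ICU mortality is a recognisable endpoint, and a few words could make it consistent. That would repair the definition. It would leave open the question in the aim, which concerns mortality in septic patients without restriction to the ICU.

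**Conclusion.** The point holds as an inconsistency of definition, with a dependence on discharge timing that remains under the reading most favourable to the sponsor. The overlap and the missing class follow from the text alone.

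The numerical effect is hypothetical. At an assumed 30% true mortality and 30 per arm it runs from no false difference (equal post-discharge shares), through 3 points and 5.7% rejection (10% versus 20%), to 12 points and 20.2% rejection (10% versus 50%). A reader might infer that a false benefit of 6 to 12 points is to be expected. The documents do not support this: it needs three to five times the control share of deaths to fall after discharge in the fluoxetine arm, and the protocol gives neither a mortality rate nor any such share.

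Mortality is a secondary outcome on which neither sample size calculation rests, so no planned number changes. This should be fixed as a cheap improvement; it does not undermine the trial as a whole.

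**What to change.** In the secondary outcome line and in Clinical Data (Final outcome):

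- Define mortality as death from any cause by day 28 after randomisation, wherever it occurs.
- Replace the survivor and non-survivor classes with one day-28 status per patient: dead, alive in ICU, or alive out of ICU. Recovery plays no part in this classification.
- Obtain day-28 vital status for patients discharged from the ICU, from the hospital record or by one telephone call.
- Report ICU mortality, defined as death in the ICU within 28 days, alongside it.

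The cost is the change of wording and one check per discharged patient, at most 60. The downside is that a few discharged patients may not be reached, and their status would be missing.

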### **Application of APACHE II and SOFA Scoring Systems:**

- APACHE II score to be evaluated on study day 1.

- SOFA score to be evaluated on study day 1 and serially every day until ICU discharge or death or up to 28 days.

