## Exclusion Criteria:

- Patients with Late septic shock at presentation with multiple organ failure
- APACHE II score on admission >25
- Preexisting liver cirrhosis
- patients with prolonged QT interval or premature ventricular beats
- Preexisting end-stage renal disease
- Pregnancy
- History of allergy to fluoxetine
- Patients with malignancies
- Uncontrolled hemorrhage
- Burns
- Previous steroid therapy
- Death within 24 hours of ICU admission
- Concurrent use of MAO inhibitors or linezolid or any drugs increase QR interval like flecainide
- History of seizures
- Age more than 65 years

Patients will be recruited after admission to the Ain Shams University Hospital. Randomization will be performed using computer-generated random number tables in opaque sealed envelopes prepared by an anesthesiologist who will not participate in the study. Patients will be randomly divided into two groups using a computer-generated random number chart:

- **Group 1:** Receiving conventional sepsis therapy alone according to our hospital protocol (summarized as the following): -
- Initial Resuscitation:

- Patients with sepsis-induced tissue hypoperfusion with suspicion of hypovolemia to achieve a minimum of 30 mL/kg of crystalloids.
- The goals of initial resuscitation of sepsis-induced hypoperfusion included all of the following:
  - MAP  $\geq$  65 mm Hg.
  - Urine output  $\geq$  0.5 ml/kg/hr.
  - CVP 8–12 mm Hg.
  - Central venous oxygen saturation (ScvO2) 70%.
- Diagnosis
- Cultures including blood cultures before antimicrobial therapy if no delay in the start of antimicrobial.
- Antimicrobial therapy
- Iv broad spectrum (one or more anti-infective drug) to cover all likely pathogen according to site of infection and hospital antibiogram.
- Source control
- Source of sepsis should be identified, and intervention should be taken as soon as possible to control it (e.g. surgical drainage and change of infected lines)
- Vasopressor
- If adequate fluid resuscitation therapy was not able to restore hemodynamic, Vasopressor therapy initiated to target a mean arterial pressure (MAP) of 65 mm Hg.
- Norepinephrine as the first-choice vasopressor, epinephrine added to and potentially substituted for norepinephrine when an additional agent is needed to maintain adequate blood pressure
- Corticosteroids
- If adequate fluid resuscitation and vasopressor therapy are not able to restore hemodynamic stability, IV hydrocortisone at a dose of 200 mg/day.

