### Statistical Analysis:

- Results will be expressed as mean  $\pm$  standard deviation or number (%). Comparison between categorical data will be performed using the Chi-square test. Comparison between different numerical data in the two studied groups will be performed using an unpaired t-test. Comparison between different times of measurements and baseline within the same group will be performed using repeated measure ANOVA. The SPSS computer program will be used for data analysis. P value less than 0.05 will be considered significant.

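### Day-1 APACHE II is collected in every patient, but all between-group tests are fixed as unadjusted, which gives up some precision and leaves chance severity imbalance uncorrected

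*Protocol*

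**What the plan says.** - **Score collected.** Protocol, Application of APACHE II and SOFA Scoring Systems: "APACHE II score to be evaluated on study day 1". SOFA is scored on day 1 and daily afterwards.
- **Score at eligibility.** Protocol, Exclusion Criteria: patients with "APACHE II score on admission >25" are excluded. The protocol does not say whether the admission score and the day-1 score are the same measurement.
- **Randomisation.** Same section: "Patients will be randomly divided into two groups using a computer-generated random number chart". No stratification by severity is described.
- **Outcomes.** Listed after the Group 2 regimen: the primary is "vasopressor dose" and the secondary is "ICU Mortality & Organ dysfunction". Clinical Data adds the need for, and duration of, ventilation and vasopressor support, and the need for hemodialysis.
- **Tests.** Protocol, Statistical Analysis: "Comparison between categorical data will be performed using the Chi-square test" and "Comparison between different numerical data in the two studied groups will be performed using an unpaired t-test". Protocol, Statistical Analysis and Sample Size: "Tests of significance (Chi-square, student's t-test, or Mann Whitney's test) will be used according to the normality of the data". Repeated-measures ANOVA is reserved for change within a group. Neither section names a covariate or a regression model.

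**The concern.** Severity at entry is handled neither in the randomisation nor in the between-group tests, although a general severity score is taken in every patient. Serial SOFA could at least be adjusted for its own day-1 value. Death, hemodialysis and the durations of vasopressor and ventilatory support have no baseline of their own, so for them a general severity measure is the natural covariate.

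Two things are at stake. One is precision in a trial of about 26 to 30 patients per arm. The other is how the result can be read if the arms turn out to differ in severity: an adjustment chosen after seeing the baseline table would look data-driven, whereas one stated in advance would not.

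**Working it through.** **Inputs.** From the protocol: effect size 0.8, α = 0.05, power 0.80 and 26 per group (Statistical Analysis and Sample Size, set for SOFA); two-sided testing (Sample Size Calculation); 60 patients (Study Population), taken here as 30 per arm. Not in the protocol: the correlation ρ between APACHE II and any outcome. It is an assumption, shown over 0.2 to 0.5.

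**1. The protocol's own figure.** For an unadjusted two-sample t-test with d = 0.8, the exact (noncentral t) solution is 25.52 per group, so 26, with power 80.7%. The stated 26 reproduces, and it assumes no adjustment.

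**2. Chance imbalance.** In units of the score's SD, the between-arm difference in means has SD √(2/n).

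| n per arm | √(2/n) | P(difference > 0.3 SD) | P(difference > 0.5 SD) |
|---|---|---|---|
| 30 | 0.258 | 2[1 − Φ(0.3/0.258)] = 25% | 2[1 − Φ(0.5/0.258)] = 5% |
| 26 | 0.277 | 28% | 7% |

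**3. What an imbalance does to the unadjusted estimate.** For a numerical outcome, the expected shift is ρ × imbalance. At 0.5 SD it is 0.3 × 0.5 = 0.15 outcome SD for ρ = 0.3, and 0.5 × 0.5 = 0.25 for ρ = 0.5.

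With 30 per arm and no true effect, the unadjusted test rejects when the difference exceeds 1.96 × 0.258 = 0.506 SD in either direction. Given the imbalance, the difference is centred on the shift with SD 0.258 × √(1 − ρ²). By normal approximation:
- ρ = 0.3: SD 0.246. Upper tail 1 − Φ((0.506 − 0.15)/0.246), plus a small lower tail, gives 7.8%.
- ρ = 0.5: SD 0.224. Upper tail 1 − Φ((0.506 − 0.25)/0.224), plus a small lower tail, gives 12.6%.

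These rates are conditional on that imbalance. Over all randomisations the rate remains 5%.

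**4. Precision.** Adjusting for one covariate multiplies the residual variance by 1 − ρ². Power uses a noncentral t with 2n − 3 degrees of freedom and noncentrality [0.8/√(1 − ρ²)] × √(n/2) × √((2n − 4)/(2n − 3)). The last factor allows for covariate imbalance.

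| ρ (assumed) | 1 − ρ² | Power, 26 per arm | Power, 30 per arm |
|---|---|---|---|
| unadjusted | 1 | 80.7% | 86.1% |
| 0.2 | 0.96 | 81.5% | 86.9% |
| 0.3 | 0.91 | 83.5% | 88.6% |
| 0.4 | 0.84 | 86.3% | 90.9% |
| 0.5 | 0.75 | 89.8% | 93.6% |

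The 0.8 was set for SOFA. The protocol gives no standardised effect for vasopressor dose, ventilation or death, and its shock-duration figure comes without an SD. The table therefore shows how the gain depends on ρ; it does not state the gain for the outcomes at issue.

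**The case against.** **The choice of covariates may be left to a statistical analysis plan.** That would answer silence. Here the protocol names the between-group tests in two places, and all of them are unadjusted. The point concerns a stated choice.

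**The unadjusted tests are valid.** This stands. Randomisation makes them unbiased, and their p-values already allow for chance imbalance. A reader might infer that the planned comparisons are biased or have an inflated error rate. They do not; the rates in step 3 hold only once a given imbalance has occurred.

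**The gain may be small.** This also stands. At ρ = 0.2 it is less than one power point. Excluding admission scores above 25 narrows the score's range and may lower its correlation with outcome.

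**APACHE II is not left out of everything, and it is not the only candidate.** Correct. The general rule for numerical data would cover describing and comparing day-1 APACHE II between groups, so it would be too strong to say that the score enters no analysis. What is missing is its use in the outcome comparisons. Day-1 SOFA and day-1 lactate are also collected and could serve. APACHE II is a reasonable choice, but not the only possible one.

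**Adjustment can be done badly.** This shapes the remedy. The protocol does not say that the day-1 score precedes the first dose, and a score taken after dosing would be a post-randomisation covariate. Support durations may be zero or cut short by death, so a plain linear model is doubtful for them. Ordinary logistic adjustment for death would target a conditional odds ratio.

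**Conclusion.** The point holds as one of efficiency and of protection against chance imbalance, not of validity. Mean APACHE II would differ by more than 0.3 SD in about one trial in four and by more than 0.5 SD in about one in twenty, at 30 per arm. The planned tests would leave any such difference uncorrected.

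The power gain cannot be fixed from the documents. In the SOFA illustration at 26 per arm it runs from 0.8 points (ρ = 0.2) to 9.1 points (ρ = 0.5), and the lower end is plausible given the exclusion of high scores. The change is worth making because it needs no new data, but it is an improvement and does not repair an invalid test.

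**What to change.** In Protocol, Statistical Analysis, state the following before unblinding:

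- APACHE II, calculated from data before the first study dose, is the single severity covariate for outcomes without their own baseline. Say whether this is the admission score used for eligibility.
- Death and other yes/no outcomes: a risk difference standardised over APACHE II.
- Vasopressor dose, and vasopressor and ventilation outcomes: a regression on treatment and APACHE II. Where durations are skewed, contain many zeros or are cut short by death, use a covariate-adjusted rank or ordinal model in place of a plain linear one.
- The unadjusted tests remain as supporting results.

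**Cost.** Wording only, with no extra patients, visits or assays. The analysis becomes slightly more complex and uses one degree of freedom. With few deaths expected, the model should stay at one covariate.

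**Separate matter.** The protocol gives vasopressor dose as primary in the outcome list and SOFA in Statistical Analysis and Sample Size, and bases Sample Size Calculation on shock duration. These must be reconciled before the adjusted primary model can be written.
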